# Postoperative analgesic effect of acupotomy combined with patient-controlled analgesia in patients undergoing video-assisted thoracoscopic surgery: a study protocol for a randomized controlled trial

**DOI:** 10.1186/s13063-020-04926-7

**Published:** 2020-12-04

**Keywords:** Acupotomy, Patient-controlled analgesia, Video-assisted thoracoscopic surgery, Randomized controlled trial, Protocol

## Abstract

**Background:**

Postoperative acute pain is a common issue following thoracic surgery. Acupotomy is a common and safe intervention method for pain treatment in clinical practice. In previous preliminary experiments, we found that acupotomy has a good clinical effect and good safety in the treatment of pain after thoracoscopic surgery. However, due to a lack of a rigorous design and an adequate sample size, its efficacy still requires further confirmation. The purpose of this study will be to explore the efficacy and safety of acupotomy combined with patient-controlled analgesia (PCA) for the treatment of pain after video-assisted thoracic surgery (VATS).

**Methods:**

The study will be a single-centre, parallel group, randomized controlled trial.

Seventy patients with significant pain after thoracoscopic surgery with a visual analogue scale (VAS) score ≥ 7 will be included and randomly distributed into two groups: G1, the acupotomy combined with PCA group; and G2, the conventional PCA group. The primary outcome measure is pain scores at rest and coughing evaluated with the VAS by a blinded observer in the postanaesthesia care unit (PACU) and postoperatively at 1, 2, 4, 8, 12, 24, 48, and 72 h. The secondary outcome measures are postoperative requirements for rescue analgesia, the cumulative amount of self-administered analgesics, the level of sedation (LOS), the Bruggemann comfort scale (BCS), and the functional activity score (FAS) concerning adverse effects and patient satisfaction.

**Discussion:**

This trial has the potential to identify an innovative and effective analgesic method for postoperative pain management for VATS. The findings may advocate for the inclusion of the treatment of comorbid pain after thoracoscopy in current pain management practice guidelines.

**Trial registration:**

Chinese Clinical Trial Registry ChiCTR1900027191. Registered on 4 November 2019

## Background

Postoperative acute pain is a common issue following thoracic surgery [1]. Although minimally invasive compared to the thoracotomy approach, postoperative pain arising from intercostal muscle, fascia, nerve, and visceral tissue injury after video-assisted thoracoscopic lung surgery must still be considered moderate to severe [2, 3]. Poor postoperative analgesia is not only related to reduced patient satisfaction but also leads to impairment of postoperative cardio-pulmonary function and further deterioration of the condition [4, 5]. For example, severe postoperative pain will increase the risk of long-term chronic pain, sympathetic activation may lead to cardiovascular adverse events (AEs), slow activity will increase the risk of thromboembolism events, and if the patient does not recover for a long time, he or she may have anxiety, depression, and other psychological problems [6]. The medical costs and hazards of postoperative pain, including health care costs and medical resource utilization, daily activity restrictions, reduced quality of life, and an increased risk for mortality, inflict a considerable burden on patients, families, and health care systems.

Patient-controlled analgesia (PCA) is a personalized strategy involving various opioids that allows patients to administer analgesics as needed and has been demonstrated to be effective for postoperative pain management under diverse conditions [7, 8]. In addition, a series of reports have shown that other effective analgesic techniques exist, including intraspinal block, peripheral nerve block, wound infiltration, and systemic nonsteroidal anti-inflammatory drug (NSAID) administration [9–11].

However, most of these modalities are technically complex and present a high risk and/or carry a high risk of serious side effects such as epidural haematomas, dural puncture, nerve injuries, pneumothorax, hypotension, infection, respiratory depression, cough suppression, coagulopathy, local anaesthetic toxicity, and renal impairment [12, 13]. Therefore, no analgesic drug can be used alone to effectively treat severe pain without side effects. Once again, multimodality pain management is found to be superior. Enhanced Recovery After Surgery (ERAS) is a multimodal, multidisciplinary approach to the treatment of surgical patients with the aim of enhancing the quality of recovery after surgery [14]. The role of pain management in ERAS pathways is fundamental considering the importance of containing surgical stress, reducing pain-related complications, and accelerating recovery [15–17]. In regard to pain management, ERAS promotes the adoption of a multimodal strategy that is tailored to individual patients [18]. However, no consensus is currently available on the best strategy for treating pain after video-assisted thoracic surgery (VATS).

Acupotomy, which is widely used in Korea and China as a special form of acupuncture with characteristics of surgical procedures, is widely used for musculoskeletal conditions and is considered an excellent treatment for pain relief [19]. The analgesic effect of acupotomy has been recognized by many clinicians [20]. Acupotomy can relieve muscle spasms, relax compressed nerves, promote local microcirculation, and thus alleviate ischaemia-related pain. An animal study also showed that extracellular signal-regulated kinase activation in the skin layer contributes to the analgesic effect of acupuncture [21]. Moreover, in previous preliminary experiments, we found that acupotomy has a good clinical effect and good safety in the treatment of pain after thoracoscopic surgery. The preliminary study did not set strict inclusion and exclusion criteria, had no randomized control, and included simple outcome indicators. However, due to the lack of a rigorous design and an adequate sample size, the efficacy requires further confirmation.

Thus, in this trial, we combined acupotomy with PCA to form a multimodal analgesia regimen and designed a randomized controlled trial to explore its efficacy and safety in the treatment of pain after VATS.

## Methods

### Study design and setting

This study will use a single-centre, parallel group, randomized controlled trial to explore the efficacy and safety of acupotomy combined with PCA for the treatment of pain after VATS. The study will be carried out at Fujian Provincial Hospital and has been registered with the Chinese Clinical Trial Registry (ChiCTR1900027191).

After eligibility screening and written informed consent provision, eligible participants after thoracoscopic surgery will be randomly distributed into two postoperative analgesia groups: G1, the acupotomy combined with PCA group; and G2, the conventional PCA group. In addition to the abovementioned analgesic regimen, all subjects will receive conventional postoperative treatment, including health education and conventional medical therapy. This protocol design adheres to the Standard Protocol Items: Recommendations for Interventional Trials (SPIRIT) Checklist (Additional file 1). The flow diagram for this trial is presented in Fig. 1.

**Fig. 1 Fig1:**
[figure not shown]
Flow diagram of the study design

### Sample size

Based on the results of our preliminary experiments, the visual analogue scale (VAS) scores (mean difference ± SD) at rest for postoperative day 1 were 3.47 ± 1.39 in the conventional PCA group and 2.34 ± 1.21 in the acupotomy combined with PCA group. We input these data into the G-power 3.1.9.2 software (developed by the University of Düsseldorf, Germany) to calculate the sample size. We obtained a calculated effect size of 0.867 for this outcome after the intervention. A sample size of 70 participants is required to sufficiently detect a target effect size (0.8) with a type 1 error of 5% (*α* = 0.05). Therefore, 70 participants will be recruited, with 35 participants in each group.

### Participants and eligibility criteria

Competent doctors will strictly screen qualified subjects according to inclusion and exclusion criteria.

Seventy patients with lung cancer, an American Society of Anesthesiologists physical status I–II, an age of 30–70 years, and a VAS score ≥ 7 who are selected for VATS lobectomy will be recruited for this clinical study. They will also be required to be able to communicate well and understand how to score their pain level. All eligible participants who meet the study inclusion criteria will be identified through the Division of Thoracic Surgery. The study exclusion criteria are coagulation disorders; neuropathy; infections at the site of acupotomy; obesity (body mass index, BMI > 30 kg/m^2^); clinically significant neurological, cardiovascular, renal, and hepatic diseases; an inability to remove the tracheal catheter or to correctly use the PCA pump after surgery; psychiatric illnesses that would interfere with the perception and assessment of pain; and pain-killer use within a week before surgery.

We will have dedicated researchers to screen existing institutional registry records and databases and to work closely with the thoracic surgeons to identify qualified participants. Once eligibility is established, the research staff will contact eligible participants or their families and explain the purpose and significance of this study, provide full explanations to eliminate participants’ doubts, and ascertain interest in enrolment. If a participant agrees to enrol, informed consent will be obtained. Participants will undergo baseline assessments following informed consent provision. A CONSORT diagram of participant recruitment is shown in Table 1.

**Table 1 Tab1:** Trial process chart

Items	Before enrollment -2-1 (weeks)	PACU	Postoperative 1 h	Postoperative 2 h	Postoperative 4 h	Postoperative 8 h	Postoperative 12 h	Postoperative 24 h	Postoperative 48 h	Postoperative 72 h
Inclusion criteria	×									
Exclusion criteria	×									
Informed consent	×									
Randomization and allocation	×									
**Pain scores** (VAS)		×	×	×	×	×	×	×	×	×
Postoperative requirements for rescue analgesia		×	×	×	×	×	×	×	×	×
LOS		×	×	×	×	×	×	×	×	×
BCS		×	×	×	×	×	×	×	×	×
FAS		×	×	×	×	×	×	×	×	×
Cumulative amount of self-administered analgesics								×	×	×
Adverse events		×	×	×	×	×	×	×	×	×
Patients’ satisfaction								×	×	×

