### Study intervention

#### Interventions, anaesthesia, and patient-controlled analgesia

All patients will be expected to avoid preoperative use of pain medication. After entering the operating room, clinicians will regularly monitor the patients’ blood pressure, electrocardiography, pulse oxygen saturation (SpO_2_), and end-tidal carbon dioxide tension (PETCO_2_).

Then, patients will receive general anaesthesia under a standard protocol. General anaesthesia will be induced with 0.05 mg/kg of midazolam, 2–4 μg/kg of fentanyl, and 2 mg/kg of propofol intravenously. Tracheal intubation will be facilitated with rocuronium bromide 0.6 mg/kg. If necessary, we will repeat intubation. We will use 1–2% sevoflurane to maintain anaesthesia. During the surgery, patients will intravenously receive propofol and remifentanil at doses of 2–2.5 μg/kg and 3–4 μg/kg, respectively. In addition, we will continuously administer cisatracurium besylate to maintain muscle relaxation. The oxygen concentration will be adjusted according to the arterial blood gas value of the partial arterial blood oxygen concentration value. PETCO_2_ will be controlled between 35 and 40 mmHg. A left-sided double-lumen endobronchial tube will be inserted under the premise that the tube size matches the left mainstem bronchial diameter. We will confirm the correct tube position with the help of a stethoscope and flexible fibreoptic bronchoscopy. At 30 min before the end of the operation, we will give the patients 5–10 mg of dezocine intravenously. Patients in the conventional PCA group will be immediately connected to an intravenous self-control analgesia pump containing 2 μg/ml of sufentanil and 8 mg of ondansetron diluted in 100 ml of 0.9% saline after surgery. The initial loading dose will be 2 ml, the background dose will be 2 ml/h, the single PCA dose will be 0.5 ml, and the locking time will be 15 min. Patients will not be treated with other medical analgesics. If special requirements emerge, the study will record the specific medication time, the drug name, each dose, the total dosage, and other information in detail. Patients in the acupotomy combined with PCA group will be treated with acupotomy before PCA treatment.

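### The stated order of eligibility, consent and randomization cannot be followed, because VAS ≥ 7, extubation and pump use are known only after surgery

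*Protocol article*

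**What the plan says.** Four parts of the protocol article bear on the order of events.

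- **Participants and eligibility criteria, text.** Staff are to "screen existing institutional registry records and databases and to work closely with the thoracic surgeons to identify qualified participants". Then: "Once eligibility is established, the research staff will contact eligible participants or their families", to explain the study and gauge interest. Next, "If a participant agrees to enrol, informed consent will be obtained", and baseline assessments come after consent. The population is described as patients with "a VAS score ≥ 7 who are selected for VATS lobectomy will be recruited for this clinical study", with no time given for the score. One exclusion criterion is "an inability to remove the tracheal catheter or to correctly use the PCA pump after surgery".
- **Abstract, Methods.** The pain criterion is placed after the operation: "Seventy patients with significant pain after thoracoscopic surgery with a visual analogue scale (VAS) score ≥ 7 will be included".
- **Study design and setting.** Screening and written consent come first, then randomization of participants who have had their surgery. Whether consent precedes the operation is not said.
- **Table 1.** The rows for inclusion criteria, exclusion criteria, informed consent, and randomization and allocation are each marked once, in the column headed "Before enrollment -2-1 (weeks"). The next column is the PACU, where the first VAS is recorded.

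**The concern.** The text makes consent wait for eligibility. If eligibility means all the listed criteria, it cannot be complete until the patient is awake, extubated, able to work the pump and reporting a VAS of at least 7. Table 1 has eligibility, consent and randomization finished one to two weeks earlier. A site cannot do both, and an ethics reviewer cannot tell which is meant.

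Two things are at stake, one under each reading.

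- **Under the literal text,** consent to a needling procedure done without skin anaesthesia (Acupotomy treatment) is first sought from patients who have just had general anaesthesia and are in severe pain. Consent given then is open to challenge.
- **Under Table 1,** patients are allocated before anyone knows whether they meet the criterion that defines the population. Those whose VAS stays below 7, or who cannot be extubated or cannot use the pump, would then be either excluded after randomization or kept despite being ineligible. The Statistical analysis section intends to analyse all allocated subjects with available data, so the first course breaks that rule and the second changes the population under study.

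**Working it through.** The point concerns sequence. The plan gives no figure to reproduce, so the check sets the statements side by side.

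**Step 1. When can each criterion be known?**

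| Criterion | Source | Earliest time knowable |
|---|---|---|
| Lung cancer, ASA status I–II, age 30–70, selected for VATS lobectomy, able to communicate and to score pain | Participants and eligibility criteria | Before surgery |
| VAS ≥ 7 | Same section (no time given); Abstract, Methods (after thoracoscopic surgery) | After surgery; first scheduled VAS is in the PACU (Table 1; Outcome measures) |
| Tracheal tube can be removed | Participants and eligibility criteria, exclusions | After surgery |
| PCA pump used correctly after surgery | Same exclusion | After surgery |

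The inclusion list and the exclusion list therefore each hold at least one item that cannot be settled before the operation. The conclusion does not depend on the pain score alone. If VAS ≥ 7 were somehow read as preoperative, the exclusion would still be explicitly postoperative. The Discussion also describes the population as having poorly controlled postoperative pain, which supports the Abstract's timing.

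**Step 2. What order does the text give?** Eligibility established → contact and explanation → consent → baseline assessments. Combined with Step 1, and with eligibility taken to mean all the criteria, consent falls after surgery.

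**Step 3. What order does Table 1 give?** Inclusion criteria, exclusion criteria, consent and randomization all fall in weeks -2 to -1, and the PACU follows.

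**Step 4. Compare, row by row.**

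| Table 1 row (weeks -2 to -1) | Can it be done then? |
|---|---|
| Inclusion criteria | Not in full: VAS ≥ 7 is unknown |
| Exclusion criteria | Not in full: extubation and pump use are unknown |
| Informed consent | Yes in practice, but not under the text's rule that eligibility comes first |
| Randomization and allocation | Only before eligibility is complete; it also conflicts with Study design and setting, which randomizes participants after surgery |

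All four rows conflict with some other statement in the article. For three of them (both criteria rows and randomization), Table 1 is what cannot stand. For consent, Table 1's timing is workable, and the sentence in the text needs qualifying.

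**Step 5. Is there room for the literal text order after surgery?** The section on interventions has control patients connected to the pump immediately after surgery. It states no interval for contact, explanation, consent, baseline assessment and allocation. This adds strain to the literal reading but does not decide the matter.

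**The case against.** The strongest reply is that the text describes ordinary preoperative recruitment. Staff search records and work with the surgeons, and the patients are those selected for lobectomy, which is not how one first meets a patient in a recovery unit. On that view eligibility in the key sentence means the preoperative criteria, consent is taken before surgery as in Table 1, and the pain score is checked later. Study design and setting fits this too. The flow diagram is not shown and may give the order, and a journal article condenses consent procedure.

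Much of this stands. It is a plausible account of what is intended. But it requires eligibility to mean a subset of the criteria, which the article nowhere says. It also does not rescue Table 1, whose randomization row would still come before the qualifying score. This is a conflict between printed statements, not a detail left to a fuller document.

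A reader might infer several stronger points that the article does not support:

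- **Families consent on the patient's behalf.** Families are named only among those contacted and informed; consent follows when the participant agrees ("If a participant agrees to enrol, informed consent will be obtained").
- **Consent is taken in the PACU.** No time or place is stated. It is an inference from where the first VAS is scheduled, and the record-screening route points the other way.
- **The consent discussion delays treatment by a known amount.** No duration is given. A discussion held before allocation would not by itself bias the comparison between arms.
- **A postoperative discussion selects out patients who cannot take part.** Ability to communicate well is already required, so any further selection is speculative.
- **Study conduct begins before consent, because "All patients will be expected to avoid preoperative use of pain medication".** This mirrors the exclusion for pain-killer use in the week before surgery and may be usual care.

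**Conclusion.** The concern holds as a contradiction in sequence. The text ties consent to established eligibility, and eligibility has postoperative parts. Table 1 puts eligibility, consent and randomization before those parts can be observed. The rules cannot all be followed, and the passages should be reconciled.

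The extent is four rows of Table 1 and two text sections, with the pain criterion bearing on all 70 planned participants. No effect on power or on the treatment estimate can be calculated, because the article does not give the share of lobectomy patients who reach VAS ≥ 7 or say which order is used in practice.

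The conclusion rests on two readings. One is that VAS ≥ 7 is a postoperative score, as the Abstract says and the Discussion supports. The other is that eligibility in the key sentence means every listed criterion. If only preoperative criteria were meant, the consent conflict becomes a matter of unclear wording, but the conflict over Table 1's criteria and randomization rows remains.

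**What to change.** **Text (Study design and setting; Participants and eligibility criteria).** State one order in both places:

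1. Written consent is obtained from the patient before surgery, from all VATS lobectomy candidates who meet the preoperative criteria.
2. The postoperative criteria (VAS ≥ 7, extubation, pump use) are confirmed after surgery.
3. Allocation takes place only then.

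Give VAS ≥ 7 its time point in the eligibility section as well as in the Abstract. Word the pump criterion so that it can be judged before allocation. The acupotomy group starts PCA only after acupotomy, so observed pump use in that arm would otherwise be a criterion assessed after randomization. The statement that control patients are connected immediately after surgery must be reconciled with the sequence adopted.

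**Table 1.** Keep consent in the preoperative column. Split the inclusion and exclusion rows into preoperative and postoperative parts. Move randomization and allocation to after the qualifying VAS.

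**Optional.** Add a phrase saying that contact with families does not replace the patient's own consent.

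**Cost.** Wording and a revised table. Some patients will consent and then not reach VAS ≥ 7; they are not randomized and are reported as screen failures in the flow diagram. More patients must therefore be approached than the 70 randomized, by a number the article does not allow one to estimate.

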### Randomization and blinding

In this study, we will use SAS (SAS 9.2) statistical software to create a randomization sequence generated by an independent statistician. The randomization sequence will assign patients on the basis of a 1:1 ratio to either the intervention group (acupotomy combined with PCA group) or the control group (conventional PCA group). The allocation sequence (containing random numbers and allocation and intervention information) will be concealed from the researchers who are responsible for enrolling and assessing participants in sequentially numbered, opaque, sealed, and stapled envelopes. The project manager will evaluate the baseline information of eligible participants and then inform them of the group to which they are assigned. Study personnel involved in recruitment, screening, data collection, and data entry will be blinded to group assignments. Due to the nature of the intervention, blinding the participants is impossible.

### Study intervention

#### Interventions, anaesthesia, and patient-controlled analgesia

All patients will be expected to avoid preoperative use of pain medication. After entering the operating room, clinicians will regularly monitor the patients’ blood pressure, electrocardiography, pulse oxygen saturation (SpO_2_), and end-tidal carbon dioxide tension (PETCO_2_).

Then, patients will receive general anaesthesia under a standard protocol. General anaesthesia will be induced with 0.05 mg/kg of midazolam, 2–4 μg/kg of fentanyl, and 2 mg/kg of propofol intravenously. Tracheal intubation will be facilitated with rocuronium bromide 0.6 mg/kg. If necessary, we will repeat intubation. We will use 1–2% sevoflurane to maintain anaesthesia. During the surgery, patients will intravenously receive propofol and remifentanil at doses of 2–2.5 μg/kg and 3–4 μg/kg, respectively. In addition, we will continuously administer cisatracurium besylate to maintain muscle relaxation. The oxygen concentration will be adjusted according to the arterial blood gas value of the partial arterial blood oxygen concentration value. PETCO_2_ will be controlled between 35 and 40 mmHg. A left-sided double-lumen endobronchial tube will be inserted under the premise that the tube size matches the left mainstem bronchial diameter. We will confirm the correct tube position with the help of a stethoscope and flexible fibreoptic bronchoscopy. At 30 min before the end of the operation, we will give the patients 5–10 mg of dezocine intravenously. Patients in the conventional PCA group will be immediately connected to an intravenous self-control analgesia pump containing 2 μg/ml of sufentanil and 8 mg of ondansetron diluted in 100 ml of 0.9% saline after surgery. The initial loading dose will be 2 ml, the background dose will be 2 ml/h, the single PCA dose will be 0.5 ml, and the locking time will be 15 min. Patients will not be treated with other medical analgesics. If special requirements emerge, the study will record the specific medication time, the drug name, each dose, the total dosage, and other information in detail. Patients in the acupotomy combined with PCA group will be treated with acupotomy before PCA treatment.

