### Outcome measures

When patients are transferred to the PACU, vital signs (heart rate, noninvasive blood pressure, respiratory rate, and SpO_2_) will be monitored and recorded every 5 min for at least 30 min. When the patients’ vital signs are stable and they are able to communicate easily, a series of clinical-scale evaluations and analgesia will be evaluated and recorded. The primary outcome measure of this study is the postoperative pain intensity score. Pain scores (VAS) in the PACU and postoperatively at 1, 2, 4, 8, 12, 24, 48, and 72 h at rest and coughing in each group will be assessed. The VAS ranged from 0 = no pain to 10 = unbearable pain. The mean value and standard deviation will be used for descriptive analysis. The primary outcomes of this study were the resting and dynamic pain scores, which were recorded using a VAS. The secondary outcome measures are postoperative requirements for rescue analgesia, the cumulative amount of self-administered analgesics, the level of sedation (LOS), the Bruggemann comfort scale (BCS), and the functional activity score (FAS) concerning adverse effects and patient satisfaction.

The time to the first rescue analgesic use and the cumulative amount of self-administered analgesics in the first 48 and 72 h will be recorded. The BCS, LOS, and FAS will be recorded at 1, 4, 8, 16, 24, 48, and 72 h after surgery. The LOS is recorded on a 5-point scale, with 0 indicating fully awake, 1 indicating drowsy/closed eyes, 2 indicating asleep/easily aroused with light tactile stimulation or a simple verbal command, 3 indicating asleep/arousable only by strong physical stimulation, and 4 indicating unarousable. The BCS is scored as 0, persistent pain; 1, severe pain while deep breathing or coughing; 2, mild pain while deep breathing or coughing; 3, painless while deep breathing; and 4, painless while coughing. The FAS is scored as A, not restricted; B, mild to moderately restricted; and C, severely restricted. Postoperative adverse effects such as nausea, vomiting, hypotension, hypoxemia, cardiac arrhythmia, and the complications from the drugs and technique will be recorded and treated.

Patient satisfaction will be assessed verbally at 24, 48, and 72 h after surgery using a 5-point Likert scale (5 = completely satisfied, 4 = quite satisfied, 3 = slightly dissatisfied, 2 = dissatisfied, 1 = very dissatisfied). The observer who records the postoperative data will also be blinded to the group assignments.

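### Without a refill, the 100 ml PCA pump is empty by 49 h, so 48 and 72 h self-administered consumption can miss later demand; the unaffected 24 h value is in Table 1 but not in the outcome text

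*Protocol article*

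**What the plan says.** The section on interventions, anaesthesia and patient-controlled analgesia gives a sufentanil concentration of 2 μg/ml, with the drugs "diluted in 100 ml of 0.9% saline after surgery". The settings are: "The initial loading dose will be 2 ml, the background dose will be 2 ml/h, the single PCA dose will be 0.5 ml". A minimum interval between boluses is also fixed, in these words: "and the locking time will be 15 min". All of this follows the sentence on the conventional arm. For the other arm the article says only: "Patients in the acupotomy combined with PCA group will be treated with acupotomy before PCA treatment". It neither describes nor excludes refilling or replacing the pump.

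Outcome measures lists self-administered analgesic among the secondary outcomes and gives its times: "the cumulative amount of self-administered analgesics in the first 48 and 72 h will be recorded". Table 1, under Participants and eligibility criteria, has a row "Cumulative amount of self-administered analgesics" with three marks, under 24, 48 and 72 h.

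**The concern.** Load and background infusion alone use almost the whole described volume by 48 h and exceed it well before 72 h. If the pump is filled once, the two times named in the outcome text are those at which the reservoir, and not only the patient's need, can determine the recorded amount. The arm with the heavier demand empties its pumps sooner and stops accumulating sooner, so a real opioid saving from acupotomy could look smaller than it is. The one scheduled time that the reservoir cannot affect is missing from the outcome text.

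The Discussion relies on analgesic use as an objective complement to subjective scales in a trial whose participants cannot be blinded, so the measure should reflect demand.

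**Working it through.** The article states no pump duration, so there is no figure of its own to reproduce.

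**Inputs from the article.** Fill V = 100 ml; load 2 ml; background 2 ml/h; bolus 0.5 ml; lockout 15 min, so at most 4 boluses/h, or 2 ml/h.

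**Assumptions.** One fill, and the same settings in both arms.

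**Emptying time** at a constant bolus rate b (ml/h): (V − 2)/(2 + b).
- No boluses: 98/2 = 49.0 h.
- Lockout limit: 98/4 = 24.5 h.

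**Volume needed by load and background alone.**
- By 48 h: 2 + 96 = 98 ml, leaving 2 ml, or 4 boluses.
- By 72 h: 2 + 144 = 146 ml.

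**Most that can be used by 24 h.** 2 + 48 + 48 = 98 ml (98.5 ml if a bolus is given at time 0). This is below 100 ml, so the 24 h amount is never limited.

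**72 h against 48 h.** Nothing can be delivered after 49 h, so the later value covers at most one further hour.

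**If drug volumes are added to the 100 ml** (assumed total 108 ml): emptying is at 106/4 = 26.5 h to 106/2 = 53.0 h, and (108 − 98)/0.5 = 20 boluses fit by 48 h. The pump is still empty before 72 h, and 24 h is still unaffected.

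**Effect on the difference between arms.** The article gives no bolus rates, so these are illustrations. Demand starts at b0 and either stays constant or halves every h hours. With k = ln 2/h, cumulative demand is B(t) = b0(1 − e^(−kt))/k. The pump empties at te, where 2 + 2te + B(te) = V, and the recorded value is B(min(t, te)). For b0 = 1 versus 0.5 ml/h (2 versus 1 bolus/h) and V = 100:

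| Demand | te, two arms (h) | Recorded gap (ml) | True gap at 48 / 72 h (ml) | Shrinkage at 48 / 72 h |
|---|---|---|---|---|
| Half-life 12 h | 41.1, 45.0 | 7.69 | 8.12 / 8.52 | 5% / 10% |
| Half-life 24 h | 37.5, 42.9 | 10.63 | 12.98 / 15.15 | 18% / 30% |
| Half-life 48 h | 35.2, 41.2 | 12.06 | 17.31 / 22.38 | 30% / 46% |
| Constant | 32.7, 39.2 | 13.07 | 24 / 36 | 46% / 64% |

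In the 24 h half-life row, at 2 μg/ml, the recorded gap is 21 μg of sufentanil instead of 26 μg at 48 h and 30 μg at 72 h.

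- Lower demand (0.5 versus 0.25 ml/h), half-lives 12 to 48 h: 2–16% at 48 h and 7–35% at 72 h.
- A 108 ml fill with 1 versus 0.5 ml/h, same half-lives: 2.5–25% and 7.5–42%.
- Extreme case, one arm at the lockout limit throughout (2 versus 1 ml/h, constant): the gap is 16.33 ml instead of 48 and 72 ml, or 66% and 77% smaller.
- At 24 h the shrinkage is 0% in every case.

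**Direction.** The recorded gap equals the true gap at the moment the lighter arm's pump empties, minus what the heavier arm wanted between the two emptying times. It is therefore smaller than the true gap as long as the acupotomy arm's demand does not later exceed the control arm's.

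**Definition.** If total pump volume were analysed instead of boluses, every patient would reach the same 100 ml (200 μg) by 49 h, and the 72 h difference would be zero.

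**The case against.** The strongest reply is that a single fill is inferred from silence. A journal article may leave reservoir changes to the full protocol, and scheduling consumption to 72 h makes most sense if PCA runs that long, which would require a refill. That stands: the reservoir effect is conditional, and with refills it disappears.

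A reader might infer that, with one fill, consumption is limited for every patient at 72 h and for anyone using more than four boluses by 48 h. That does not follow, because an empty pump loses only demand that arises afterwards. A patient with 10 boluses (5 ml) empties the pump at (98 − 5)/2 = 46.5 h and loses nothing if no further dose was wanted. In the 12 h half-life case the lighter arm's pump empties at 45.0 h, yet its mean recorded volume by 48 h is 8.01 ml against 8.12 ml wanted.

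The percentages also rest on assumed rates and half-lives. One could argue for declining demand from the entry criterion ("and a VAS score ≥ 7 who are selected for VATS lobectomy") and the pilot means ("at rest for postoperative day 1 were 3.47 ± 1.39 in the conventional PCA group"), but the Background says the preliminary study had no strict inclusion criteria, so its patients need not have started at 7 or above. The range therefore includes trivial effects.

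Finally, rescue analgesia is recorded separately to 72 h, and Table 1 already plans the 24 h reading. Both points limit the harm. Neither reconciles text and table or shows when a pump ran dry.

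**Conclusion.** The point holds as a minor, conditional one. If the pump is filled once and both arms share the settings, 48 and 72 h consumption can miss late demand, and the 72 h value is nearly a copy of the 48 h value. The illustrated shrinkage of about 2–46% and 7–64% (100 ml fill) shows what could happen and is not an estimate.

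A reader might also infer that the plan could create a false opioid saving, or that the main result is at risk. The documents do not support either. With equal settings the expected bias is toward no effect, and VAS through 24 h, the day 1 value behind the sample size, and the separate rescue record are unaffected.

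One part needs no assumption: Outcome measures and Table 1 disagree on whether 24 h consumption is recorded.

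**What to change.** In Outcome measures:
- Add 24 h to the consumption times, to match Table 1.
- Define consumption as the volume of patient-triggered boluses read from the pump, excluding load and background.
- Record the time at which the pump empties or is refilled.

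State how the values will be read. Without refills, 24 h is the main consumption comparison, with 48 and 72 h supportive. With refills, 48 and 72 h keep their standing.

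The cost is a short wording change and one CRF field, with no change to treatment, visits or sample size. The downside, without refills, is less weight on 48 and 72 h.
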